#### Exploratory clinical outcomes: depressive symptoms

Clinical outcomes are exploratory (Table 1). The principal exploratory clinical outcome is change in depressive symptom severity measured using MADRS-S. Depressive symptoms will be assessed at baseline (week 0) before initiation of tDCS, at week 1, at the end of the initiation phase (week 4), at week 7, and at a preoperative assessment conducted within a defined window before surgery (week 8–10+). Observed changes in depressive symptom severity will be interpreted in the context of the study’s feasibility-focused design. These analyses are not intended to establish efficacy, but rather to generate preliminary signal and variability estimates to inform future trial design.

**Table 1 tab1:** Exploratory outcomes.

Domain	Measure	Baseline	Timepoints*	Pre-op**	Post-op
Depression	MADRS-S	X	X	X	—
Spine disability	Oswestry disability index (ODI)	X	—	X	X (6 wks or 3 mos)
Pain intensity	Back pain NRS (0–10)	X	X	X	X
	Leg pain NRS (0–10)	X	X	X	X
Pain-related function	PROMIS pain interference (SF)	X	Optional	X	X
Physical function	PROMIS physical function (SF)	X	—	X	X
Opioid exposure	Baseline outpatient opioid use (MME)	X	—	—	—
Opioid utilization	Inpatient postoperative MME	—	—	—	X
	30-day outpatient postoperative MME	—	—	—	X

*Week(s) 0, 1, 4, 7, 10, and preoperatively (as applicable). **≤7 days before surgery.

#### Exploratory clinical outcomes: perioperative recovery

Additional exploratory outcomes are included to examine whether preoperative home-based tDCS exposure is associated with changes in pain-related disability, functional status, and analgesic utilization in elective lumbar spine surgery candidates. Exploratory analyses will examine associations between tDCS exposure—both by pre-specified exposure tier and as a continuous measure of completed sessions—and changes in these outcomes.

Spine-specific disability will be assessed using ODI, administered at baseline, during the preoperative assessment window, and at a single exploratory postoperative time point. Pain intensity will be measured using 11-point numeric rating scales (NRS) for both back pain and leg pain. Pain-related functional impact will be assessed using the PROMIS Pain Interference short form, and overall physical function will be assessed using the PROMIS Physical Function short form.

Analgesic utilization will be evaluated using standardized morphine milligram equivalent (MME) calculations. Exploratory opioid outcomes will include baseline outpatient opioid exposure prior to initiation of tDCS, inpatient postoperative opioid utilization from surgery to hospital discharge, and cumulative outpatient opioid utilization during the early postoperative period.

#### Safety end points

Safety outcomes include the incidence and severity of adverse events (AEs) and serious adverse events (SAEs), as well as intervention discontinuations and protocol deviations attributable to tolerability or device use. Adverse events of interest include commonly reported minor effects such as scalp irritation, headache, and tinnitus. Safety outcomes will be summarized overall and, where relevant, by intervention phase.

### Analysis plan

Analyses will be conducted primarily to evaluate feasibility and acceptability, with clinical and perioperative outcomes analyzed on an exploratory, hypothesis-generating basis. All analyses will be prespecified and reported descriptively where appropriate, consistent with the pilot nature of the study.

#### Feasibility criteria

Feasibility will be evaluated across recruitment, initiation/adherence, acceptability, retention, and safety domains. The study will be considered feasible if (1) ≥ 60% of initiated participants achieve the minimum preoperative exposure target (Tier A, ≥15 total sessions completed before surgery); (2) overall retention is ≥50% for the preoperative assessment and ≥40% for the 30-day postoperative follow-up; (3) acceptability is supported by a mean treatment satisfaction/usability score ≥4/5 and ≤20% discontinuation attributable to device-related adverse effects or burden; and (4) safety is supported by no device-related serious adverse events, ≤10% escalation for emergent psychiatric concerns, and an adverse event profile consistent with expected transient tDCS effects (e.g., mild headache or scalp discomfort). Feasibility outcomes will be summarized descriptively with 95% confidence intervals and used to refine recruitment workflows, dosing schedules, and monitoring procedures for a subsequent randomized trial.

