**Figure 2 fig2:**
[figure not shown]
User wearing the flow neuroscience headset (Flow neuroscience patient sign-up, 2026). Source: Images were reproduced, with permission, from the parent company - Flow Neuroscience.

We hypothesize that most enrolled participants will be able to initiate treatment, defined as completion of the tDCS initiation phase within the first 3 weeks, and that a substantial proportion will achieve at least the minimum pre-specified treatment exposure before surgery. We further hypothesize that the intervention will be acceptable and well-tolerated, as reflected by high adherence, low rates of discontinuation due to adverse effects, and favorable participant-reported satisfaction.

A key exploratory clinical objective of the study is to assess preliminary changes in depressive symptom severity associated with preoperative home-based tDCS. The principal exploratory clinical outcome is change in depressive symptoms, measured using the self-reported Montgomery–Åsberg Depression Rating Scale (MADRS-S), consistent with prior home-based tDCS studies. We hypothesize that participants will demonstrate a reduction in depressive symptom severity from baseline to the preoperative assessment, with measurable improvement evident following completion of the intensive initiation phase.

Additional exploratory objectives include examining whether preoperative tDCS exposure is associated with changes in perioperative recovery-relevant outcomes. These exploratory outcomes include spine-related disability measured using the Oswestry Disability Index (ODI); back and leg pain intensity assessed via numeric rating scales; pain-related function measured using the PROMIS Pain Interference short form; and overall physical function measured using the PROMIS Physical Function short form. Opioid exposure will be assessed using standardized morphine milligram equivalent (MME) calculations, including baseline outpatient opioid use and postoperative opioid utilization across inpatient and outpatient settings.

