**Figure 3 fig3:**
[figure not shown]
CONSORT-style participant flow diagram. Participants are identified through spine surgery clinic schedules and screened for eligibility. Enrolled participants initiate home-based tDCS and are classified by pre-specified exposure tier based on the number of sessions completed. Following the intervention period, participants who proceed to elective lumbar spine surgery enter postoperative follow-up. Participants who do not proceed to surgery are followed for pre-operative and intervention-related outcomes only; postoperative recovery endpoints are not collected for this subgroup. All participants are included in the primary as-treated analysis by exposure tier achieved. Source: Images were reproduced, with permission, from the parent company - Flow Neuroscience.

The study is designed to prioritize feasibility and acceptability, with an exploratory assessment of changes in depressive symptom severity. Because the interval between surgical decision-making and operative intervention varies across patients, the intervention is delivered using a dose-to-time model with pre-specified exposure tiers based on the number of tDCS sessions completed before surgery.

As a pilot study, the design aims to (1) operationalize home-based neuromodulation within a perioperative spine surgery workflow, (2) quantify feasibility, acceptability, and safety, and (3) generate preliminary estimates of symptom change and variability to inform the design of future controlled trials. The protocol is reported in accordance with SPIRIT recommendations for interventional trial protocols (Supplementary Table S1).

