### Dosing schedule

All participants initiate treatment using a standardized dosing cadence derived from prior Flow Neuroscience trials. During the initiation phase (weeks 1–3), participants complete five tDCS sessions per week (15 sessions total). Beginning in week 4, participant’s transition to a maintenance phase of three sessions per week, continuing until the date of surgery or a maximum treatment duration of 10 weeks, whichever occurs first.

Because the interval between enrollment and surgery varies across participants, the total treatment duration is variable as well. The minimum planned exposure is 4 weeks, with a target exposure of 6–10 weeks when feasible. A treatment session is classified as complete if the full 30-min stimulation protocol is delivered, as recorded by the device, in accordance with protocol parameters. Sessions interrupted or terminated before 30 min will be classified as partial (≥20 min of stimulation delivered) or incomplete (<20 min of stimulation delivered). Only sessions classified as complete will count toward exposure tier classification. Partial and incomplete sessions will be documented and reported descriptively, with sensitivity analyses examining whether their inclusion materially affects feasibility metrics.

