### Exposure tiers

To accommodate variability in surgical scheduling, participants are categorized based on the number of completed tDCS sessions before surgery:

Tier A (initiation complete): ≥15 sessions (~3–4 weeks)Tier B (initiation + ≥ 1 maintenance week): ≥21 sessions (~5 weeks)Tier C (full exposure): 36 sessions (10-week regimen)

Participants will be analyzed on an as-treated basis, by the exposure tier achieved, regardless of intended treatment duration or if they proceeded with surgery.

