### Onboarding and monitoring

Participants will receive standardized onboarding and device training, including in-clinic instruction when feasible and structured digital training materials. Training will emphasize correct headset placement and session initiation. Adherence will be monitored using application-generated usage logs, including session date, time, and completion status, which are accessible to the research team. Participants may be contacted weekly during the preoperative period to assess tolerability, address technical issues, review adherence, and screen for emerging concerns.

Deviations from the intended treatment schedule (e.g., missed sessions, delayed or rescheduled surgery dates) will be documented to support interpretation of feasibility outcomes and planned sensitivity analyses.

Tolerability will be explicitly assessed during onboarding sessions. Participants who experience intolerable adverse effects at the protocol-specified 2 mA intensity during initial onboarding (e.g., severe scalp discomfort, headache not relieved by standard measures, or other adverse effects leading to participant request to discontinue) will be documented as onboarding-phase discontinuations.

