#### Sample size justification

The sample size is selected to provide reasonable precision around key feasibility metrics (treatment initiation, tier attainment, and adherence), and to generate preliminary estimates of variability in symptom change to inform a future randomized trial. With *n* = 20 participants who initiate tDCS, an observed feasibility proportion in the range expected for home-based neuromodulation (e.g., 60%–80%) would yield a 95% confidence interval width of ~0.34–0.40 (approximately ±0.17–0.20), which is adequate for feasibility decision-making and for informing go/no-go thresholds for subsequent trials. To account for anticipated attrition and scheduling-related drop-off before surgery, we will enroll *n* = 24–25 participants, targeting *n* = 20 evaluable participants who initiate treatment and contribute preoperative outcome assessments.

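### The 60% go criterion counts only initiated participants, a term the protocol defines so that the criterion cannot fail and elsewhere uses so that enrolled never-starters drop out

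*Protocol article*

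**What the plan says.** All references are to the Protocol article.

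- **Feasibility criteria.** The study is judged feasible if, among other conditions, at least 60% "of initiated participants achieve the minimum preoperative exposure target", which is given as Tier A, 15 or more sessions in total before surgery.
- **Objectives and hypotheses.** The hypothesis is that most enrolled participants will be able to "initiate treatment, defined as completion of the tDCS initiation phase within the first 3 weeks". No other section gives an explicit definition of initiating.
- **Dosing schedule.** In the initiation phase, weeks 1 to 3, "participants complete five tDCS sessions per week (15 sessions total"). The same section opens by saying that all participants initiate treatment on a standard cadence, where the verb can only mean start.
- **Exposure tiers.** The lowest tier is "Tier A (initiation complete): ≥15 sessions (~3–4 weeks").
- **Primary outcomes.** Feasibility of initiation is the proportion of enrolled participants with at least 15 sessions in the first 21 days. Feasibility of exposure is the proportion of participants reaching each tier, with no further qualifier.
- **Analysis populations.** The primary population is the enrolled participants who initiate the intervention.
- **Figure 3 legend.** "All participants are included in the primary as-treated analysis by exposure tier achieved".
- **Sample size justification.** The plan is to enrol 24–25 to obtain 20 "evaluable participants who initiate treatment and contribute preoperative outcome assessments".
- **Onboarding and monitoring.** Participants with intolerable effects during initial onboarding "will be documented as onboarding-phase discontinuations".

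**The concern.** A go/no-go threshold needs one fixed denominator. Here the word that sets it has two meanings, and the criterion does not say which applies. On the written definition the criterion tests nothing. On the more natural meaning it leaves out people who agree to take part and never begin, which is one of the ways a preoperative home treatment can prove infeasible. The initiation primary outcome counts those same people as failures on nearly the same event. The go rule and the primary outcome could therefore point in different directions, and the protocol does not say how to reconcile them.

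**Working it through.** **1. The plan's own figures.** The Sample size justification gives a 95% interval width of about 0.34–0.40 for an observed 60%–80% with n = 20. The Wilson width is 2z·√(n·p(1−p) + z²/4) / (n + z²), with z = 1.96 and z² = 3.84.

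- p = 0.60: 3.92 × √(4.80 + 0.96) / 23.84 = 0.395.
- p = 0.80: 3.92 × √(3.20 + 0.96) / 23.84 = 0.335.

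Both ends are reproduced. Enrolment is too: 20 / (1 − 1/6) = 24 and 20 / (1 − 0.20) = 25. The stated precision is not in dispute.

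**2. The written definition.** Suppose k participants complete the 15-session initiation phase within 3 weeks. Treatment ends at surgery at the latest, so all k have at least 15 sessions before surgery and are in Tier A. The criterion is k/k = 100% for any k above zero.

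**3. Initiate read as start.** With 20 starters the bar is 0.60 × 20 = 12. Take 12 achievers, and assume every other enrolled person never started and so did not reach Tier A:

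| Enrolled | Started | Tier A / started | Tier A / enrolled |
|---|---|---|---|
| 20 | 20 | 60% | 60.0% |
| 21 | 20 | 60% | 57.1% |
| 22 | 20 | 60% | 54.5% |
| 23 | 20 | 60% | 52.2% |
| 24 | 20 | 60% | 50.0% |
| 25 | 20 | 60% | 48.0% |

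A 60% bar on 24 or 25 enrolled needs 15 achievers (0.60 × 24 = 14.4; 0.60 × 25 = 15).

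**4. Effect on the decision, as an illustration.** Assume 20 of 25 enrolled start, non-starters never reach Tier A, and the true rate among the enrolled is 50%. The rate among starters is then 0.50 × 25/20 = 62.5%.

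- Starters as denominator: P(at least 12 of 20 at 0.625) = 0.68.
- Enrolled as denominator: P(at least 15 of 25 at 0.50) = 0.21. Holding the starters at exactly 20, P(at least 15 of 20 at 0.625) = 0.18.

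With 20 of 24 starting (rate among starters 60%), the chances are 0.60 and 0.15 (0.13 with the starters held at 20).

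The documents give no expected share of never-starters. The 4–5 extra enrolees are an upper bound under the plan's own numbers, because they also allow for people who start and later drop out.

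**The case against.** The strongest reply is that the circular reading was never meant. The definition stands in a hypothesis sentence. Where the regimen, the population and the sample size are set, the word means start. A 60% bar and an expected range of 60%–80% would be pointless if the answer were always 100%. This is a good argument about intent, and I accept it. It does not remove the conflict, because the only definition on the page says otherwise and the criterion does not restate it.

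A second reply is that judging initiation among the enrolled and exposure among starters is a coherent split, and that enrolled is explicit only for the initiation domain. That is also fair; the go criterion has no 21-day window either. But the go rule contains only the starter-based proportion. The enrolled-based figure is reported and carries no threshold, so never-starters cannot affect this criterion.

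Three stronger readings are tempting, and the text does not support them.

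- A reader might infer that the evaluable participants in the Sample size justification are a further analysis denominator. They are a recruitment target. Analysis populations sets no condition on a preoperative assessment, so on the start reading a starter who drops out stays in as a failure.
- A reader might infer that onboarding discontinuations are removed from the 20% discontinuation limit. No section removes them. They arise at the protocol's stimulation intensity and are recorded as discontinuations. The text only omits to say that they count as initiated.
- A reader might infer that the exposure period has no end for participants who do not have surgery. The Dosing schedule caps treatment at 10 weeks.

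**Conclusion.** The point holds as a conflict over the denominator of a stated decision threshold. On the written definition the first go criterion is met automatically. On the probable meaning it omits enrolled never-starters, whom the initiation primary outcome includes.

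The contrast of 60% with 48% is a worst case. It assumes that 25 enrol, 20 start, and all five others never begin. With fewer never-starters the gap is smaller, and if everyone enrolled starts there is none. Even one never-starter among 21 enrolled takes 12 achievers below the bar (57.1%), so a result near the threshold can change sides. The documents do not show that the denominator would be chosen after the data are seen. They show that the wording does not settle it.

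**What to change.** 1. In Objectives and hypotheses, replace the definition of initiating with wording that participants will complete the initiation phase.
2. Define initiated once, for the whole protocol, as at least one stimulation session started, including during onboarding. Onboarding-phase discontinuations then clearly count in the discontinuation criterion.
3. Base the 60% Tier A criterion on all enrolled participants, counting never-starters as not achieved, and report the proportion among starters alongside it.
4. Bring Analysis populations and the Figure 3 legend into line with these terms.

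The change is to wording only: no new data, assessments or participants. The cost is that the observed Tier A proportion will be lower whenever someone enrols and does not start. At 24–25 enrolled the bar becomes 15 achievers, against 12 when 20 starters are the denominator. If the investigators prefer to keep starters as the denominator, they should say so in the criterion and explain why never-starting does not bear on the go decision.

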#### Analysis populations

The primary analytic population will include all enrolled participants who initiate the tDCS intervention. Participants will be analyzed on an as-treated basis, categorized according to the pre-specified exposure tier achieved before surgery. Sensitivity analyses may be performed using alternative adherence thresholds to assess the robustness of feasibility findings.

#### Sample size justification

The sample size is selected to provide reasonable precision around key feasibility metrics (treatment initiation, tier attainment, and adherence), and to generate preliminary estimates of variability in symptom change to inform a future randomized trial. With *n* = 20 participants who initiate tDCS, an observed feasibility proportion in the range expected for home-based neuromodulation (e.g., 60%–80%) would yield a 95% confidence interval width of ~0.34–0.40 (approximately ±0.17–0.20), which is adequate for feasibility decision-making and for informing go/no-go thresholds for subsequent trials. To account for anticipated attrition and scheduling-related drop-off before surgery, we will enroll *n* = 24–25 participants, targeting *n* = 20 evaluable participants who initiate treatment and contribute preoperative outcome assessments.

#### Primary analyses: feasibility and acceptability

Feasibility outcomes will be summarized using proportions and corresponding confidence intervals. These will include the proportion of participants who complete the initiation phase (≥15 sessions within 21 days) and the proportion achieving each pre-specified exposure tier before surgery. Adherence will be summarized as the proportion of prescribed sessions completed during the preoperative period. Acceptability outcomes will be summarized descriptively. System Usability Scale (SUS) scores will be reported as mean and standard deviation and classified against established benchmarks (a score >68 indicates above-average usability). Likert satisfaction items will be reported as proportions endorsing each response category. Qualitative exit-interview data will be analyzed using an established thematic-analysis framework to identify recurring themes in participant experience. Reasons for treatment discontinuation will be summarized descriptively.

#### Exploratory clinical analyses: depressive symptoms

Exploratory analyses will evaluate changes in depressive symptom severity over time. The principal exploratory clinical outcome is the change in MADRS-S score from baseline to the preoperative assessment. Change from baseline to the end of the initiation phase (week 4) will be examined as an early signal of response following intensive treatment initiation.

Longitudinal changes in depressive symptoms will be examined using mixed-effects models to account for repeated measures and variable treatment exposure. Models will include fixed effects for time and baseline symptom severity, with random effects to account for within-participant correlation. These analyses are exploratory and not powered to establish efficacy. Exploratory response and remission rates based on standard MADRS-S thresholds will be summarized descriptively at the preoperative time point.

#### Exploratory clinical analyses: perioperative recovery outcomes

Exploratory analyses will assess associations between preoperative tDCS exposure and perioperative recovery–related outcomes, including spine-related disability (ODI), pain intensity (back and leg NRS), pain interference (PROMIS Pain Interference), physical function (PROMIS Physical Function), and opioid utilization.

tDCS exposure will be modeled both categorically (by exposure tier) and continuously (as the number of completed sessions). Opioid utilization outcomes will be analyzed using standardized morphine milligram equivalents (MME), including baseline outpatient use, inpatient postoperative utilization, and cumulative outpatient use during the early postoperative period. Analyses will be descriptive and exploratory, with appropriate regression-based approaches used to examine associations while adjusting for baseline values where relevant.

